### Criteria for discontinuing or modifying allocated interventions

A discontinuation of treatment or modification of the intervention will be initiated if a patient suffers acute or severe symptom deterioration including suicidality. In this case appropriate treatment will be initiated. The intervention can also be terminated by the participants themselves at any point in time.

### Strategies to improve adherence to interventions

Within the participant information and informed consent form, patients are made aware of the importance of regular and active participation in the therapy sessions. Patients in the waitlist control group will be called after six weeks of waiting to ensure continued participation.

Via standardized checklists, which specify the contents of each therapy session, adherence to the manual is measured. The therapists indicate which parts of the manual were carried out and which were not. If parts could not be carried out, the reasons for this are recorded, e.g. the content of the lesson was too extensive for the participant due to concentration problems.

### Relevant concomitant care permitted or prohibited during the trial

Any kind of medical care and therapy is allowed during the trial except psychotherapy (beside the study intervention).

### Provisions for post-trial care

It is hypothesized that participants will benefit from the intervention and that Long/Post-COVID-symptoms will improve. Harm from trial participation is not expected. If applicable, participants will be supported in finding appropriate follow-up treatment such as inpatient psychosomatic treatment or outpatient psychotherapy.

### Outcomes

The primary outcome of the study is the feasibility of the developed intervention. We assess whether it is possible to recruit patients, to conducte the developed intervention with them, and measure the outcomes.

In addition, an estimate of the effect size in preparation of an RCT will be conducted, and the feasibility of the corresponding assessments investigated. For the later RCT the primary outcome is health-related quality of life (measured via Short-Form Health Survey-12; SF-12). Secondary outcomes are somatic symptoms (Patient Health Questionnaire-15; PHQ-15 and Long/Post-COVID symptoms), depressive symptoms (PHQ-9), anxiety (Generalized Anxiety Disorder-7; GAD-7), fatigue (Fatigue Assessment Scale; FAS), perceived stress (Perceived Stress Questionnaire-20; PSQ-20), work ability (Work Ability Score; WAS), mental well-being (WHO-Five Well-Being Index; WHO-5), illness perception (Revised Illness Perception Questionnaire; IPQ-R), symptom-related thoughts, feelings and behaviour (Somatic Symptom Disorder - B Criteria Scale; SSD-12) and work stress (Psychosocial Safety Climate-4; PSC-4). The questionnaires are used in both groups at baseline (t1), directly post-intervention (t2) and six months after baseline assessment (t3). The analysis of intervention effects compared to control group is only conducted at the end of the intervention in the primary intervention group (comparison of intra-individual improvement). Later measurements are only used to assess if the effects in the early and late (after waiting) intervention group are similar or whether the effects are maintained after the intervention phase. Additionally, adverse childhood experiences (Childhood Trauma Screener; CTS) are assessed at t1 and treatment satisfaction (ZUF-8) at t2.

Ecological momentary assessments (EMAs) will be conducted weekly using a newly developed questionnaire consisting of a set of five items. EMAs are used to track participants’ current condition (quality of life, physical/psychological well-being, concentration, everyday abilities).

As an additional part of the study, blood samples are taken at t1 and t2 to analyse changes in the IL-1Beta, IL6, TNF cytokine triad which has been associated with Long/Post-COVID-sequelae in a recent study (29).

Blood sampling is performed only for those participants who have additionally given their consent for this part of the study.

### Participant timeline

A schematic schedule for participants is depicted in **Figure 1**.

**Figure 1 f1:**
[figure not shown]
Schematic schedule for participants. *IG, Intervention group; CG, Control group.

### Sample size

A total of N = 120 participants will be assigned to the study arms, 60 to the waitlist with regular care arm and 60 to the PsyLoCo intervention arm. Case numbers are based on feasibility within a pilot trial.

### Recruitment

Patients will be recruited via specialised Long/Post-COVID outpatient clinics of the participating university hospitals, via general practitioners or via the programme’s website (https://psyloco.de/).

## Assignment of interventions: allocation

### Sequence generation

The allocation sequence will be generated in *R* using the *blockrand* package (https://cran.r-project.org/web/packages/blockrand/index.html). The randomization is stratified by study center. The allocation sequence is created using blocking with varying block sizes (4 and 6).

### Concealment mechanism

The allocation sequence will be stored in a CSV-file in a folder that is only accessible by the biometrician who creates the allocation sequence. It is uploaded to the randomization tool in RedCap. Only the responsible biometrician has access to the file. Once the project starts, the allocation sequence cannot be changed or accessed by anyone.

### Implementation

The allocation sequence will be generated by a biometrician at the Institute for Medical Epidemiology, Biometry and Informatics at the Martin-Luther-University Halle Wittenberg. The enrolment and assigning of participants will be done by the study personnel at the five study sites.

## Data collection and management

### Plans for assessment and collection of outcomes

The variables of interest are assessed via digital self-assessment questionnaires in LimeSurvey. The only exception are the cytokine values which will be examined through blood sample analysis. Blood samples are taken by certified medical personnel.

### Plans to promote participant retention and complete follow-up

Participants can terminate study participation at any time. In this case no further outcome data are collected. To ensure completion of follow-up, participants will be contacted via e-mail and reminded to fill out the questionnaire at one week and two weeks after the initial request to complete the follow-up-questionnaire. If, after three weeks, the questionnaire has not yet been completed, participants will be given a final reminder via a telephone call.

### Data management

Since data collection is digital via LimeSurvey and RedCap, the data is entered directly by the participants/therapists and exported from the databases as CSV-file without person-identifying data for use in the statistical program *R*. Both RedCap and LimeSurvey are hosted on secure servers of the Central Service “Information and Communication” (ZB IuK) of the University Clinic Halle. Only pseudonymised data is exported for analysis.

### Confidentiality

Participant data will be collected pseudonymised. For data analysis, data will be exported to the statistical program *R*. Only the study administrator can access the list containing pseudonymisation information and digitally gathered participant health-related data.

### Plans for collection, laboratory evaluation and storage of biological specimens for genetic or molecular analysis in this trial/future use

Plasma will be separated from whole blood by centrifugation at 1400 x g for 10 min. Remaining cell debris will be removed by high-speed centrifugation at 12000 x g for 10 min. Plasma samples will be stored at -80°C. Plasma cytokine levels will be quantified using bead-based multiplex flow cytometry kits from Biolegend (LEGENDplex Human B cell Panel (13-plex), Human Anti-Virus Response Panel (13-plex)). Measurements will be performed on a BD FACSCelesta flow cytometer (compare (29) for more methodological details).

## Statistical methods

### Statistical methods for primary and secondary outcomes

The statistical analysis will be conducted utilizing descriptive analysis of primary and secondary outcomes (e.g. differences in mean and median). In an exploratory fashion, mixed-effect linear regression analysis adjusted for study site (random effect) will be used to check for differences between intervention and control groups regarding intraindividual differences in the primary outcome Health-Related Quality of Life (measured by SF-12) between enrolment (t1) and post-intervention assessment (t2). Covariates will be adjusted for if misbalance in characteristics at baseline assessment is more than 20%. In the same way, secondary outcomes will be analysed. These analyses will be also conducted to assess stability of changes i.e. comparing outcomes at t2 and t3. EMAs will be analysed using analysis of variance respectively trajectories approach to detect changes over time. Immunological parameters (i.e. cytokine levels) will be analysed in the same way as primary outcome – in case of non-normal distributions, transformation will be applied.

Additional analyses will be conducted regarding feasibility of recruitment, drop-out rate, therapist adherence and participant adherence.

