### Intervention description

The psychotherapeutic intervention is based on insights from data analysis of two patient cohorts and a set of patient interviews focusing on psychosocial needs and preferences of patients suffering from Long/Post-COVID conditions. The therapeutic manual was developed in an iterative process by a team of interdisciplinary experts (i.e. clinical psychologists, psychotherapists, residents, medical specialists). Additional feedback and comments of a group of patient representatives was also implemented in the development of the intervention. The intervention will be carried out as individual therapy in 12 sessions with one session per week. The first therapeutic sessions were held mid-March 2023. The last follow-up-measures are planned end of November 2023. The 12-session intervention is divided into four modules. Module 1 focuses on coping and distress management, module 2 on somatic symptoms and pain, module 3 on chronic fatigue and affective symptoms and module 4 on stresses regarding social and work life. The psychotherapeutic manual contains treatment techniques from cognitive-behavioral, psychodynamic and systemic psychotherapeutic approaches and techniques (i.e. psychoeducation, work sheets, resource work; **Table 1**). The implementation of the manual offers a certain degree of flexibility. In addition to the components that are always carried out for each participant, there are optional components that can be applied according to individual needs.

**Table 1 T1:** Session focus and interventions for each therapeutic session.

Session	Session focus	Interventions
1	•Therapeutic relationship •Psychoeducation Long/Post-COVID	•Documentation symptoms •Documentation course of disease •Psychoeducation Long/Post-COVID
2	•Therapeutic relationship •Defining goals of therapy •Introduction relaxation techniques	•Introduction PMR •Introduction MBSR
3	•Resource work	•Resource list/case
4	•Mind-body interplay •Psychosomatic disease model	•Psychoeducation (e.g. lemon exercise) •Individual barrel model
5	•Interplay attention and bodily symptoms	•Psychoeducation •Strategies for attention re-focus
6	•Mindfulness and bodily symptoms	•Introduction mindful perception
7	•Long/Post-COVID and depressive symptoms	•Emotional triangle •Cognitive defusion
8	•Long/Post-COVID and personal values	•Activity planning according to personal values
9	•Long/Post-COVID and fatigue	•Strategies for handling of fatigue symptoms

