## Oversight and monitoring

### Composition of the coordinating centre and trial steering committee

The study is coordinated at the institutions in Munich (TU), Magdeburg and Halle (Saale). Statistical and biomedical analyses are conducted at the Institute for Medical Epidemiology, Biometrics and Informatics at the university of Halle (Saale). Psychotherapeutic interventions are conducted at the psychosomatic departments of the university hospitals in Munich (TU), Magdeburg, Tuebingen, Ulm and Freiburg. At each study site an equal number of participants will be included (n=24). The coordinating staff meets regularly every two weeks. Full staff meetings are held monthly. Therapeutic sessions will be supervised in small groups of up to five therapists once a month by an experienced and senior specialist.

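### The planned model has a random effect for site only; if therapists differ in effect, standard errors will be too small because therapist clustering exists in one arm only

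*Protocol article*

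**What the plan says.** The section on statistical methods for primary and secondary outcomes puts descriptive analysis first and then names one model, which it calls exploratory: "mixed-effect linear regression analysis adjusted for study site (random effect"). Study site is its only random effect. The response is the within-patient SF-12 change between t1 and t2, compared between arms. Secondary outcomes and cytokine levels follow the same approach. Therapists appear in that section only under adherence.

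On delivery, the intervention description states: "The intervention will be carried out as individual therapy in 12 sessions with one session per week". The oversight section adds: "Therapeutic sessions will be supervised in small groups of up to five therapists once a month". It also sets 24 participants at each of the five treating sites. Controls wait, and the Outcomes section restricts the comparison between arms to the end of the intervention in the group treated first. The sample is "60 to the waitlist with regular care arm and 60 to the PsyLoCo intervention arm", and "Case numbers are based on feasibility within a pilot trial". The article gives no number of therapists, no caseload and no ICC.

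**The concern.** Patients treated by the same therapist may have correlated outcomes. At t2 this can happen in the intervention arm only, because the waiting list has no study therapist yet. The design is therefore partially nested, and the only clustering term in the model sits at another level. A site intercept moves both arms of a site by the same amount, so it drops out of the treatment contrast. Even with one therapist per site it does not represent variance that exists in one arm alone.

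What is at stake is the stated precision of an estimate whose declared use is planning the later RCT. If that precision is overstated, planning starts from too firm a figure. The therapist variance, which the RCT would need for its own sample size, is also not among the planned outputs.

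**Working it through.** **Inputs from the protocol article.** 60 patients per arm (Sample size). 24 per site at five sites (oversight section): 5 × 24 = 120 = 60 + 60, which agrees. With 1:1 allocation stratified by centre, about 24/2 = 12 intervention patients per site. N = 120 rests on feasibility, so there is no power figure to reproduce.

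**Is sharing of therapists plausible?** To avoid it, each site would need about 12 therapists with one intervention patient each, 60 in all. The article does not say that therapists are shared, but the inference is strong.

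**Assumptions, not in the article.** Therapist ICC ρ from 0.02 to 0.10. One to five therapists per site, so m = 12, 6, 4, 3 or 2.4 patients per therapist. Total variance 1 in each arm.

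**Formulas.**
- True variance of the arm difference: [1 + (m − 1)ρ]/60 + 1/60.
- Variance under the site-only model: about 2/60.
- True SE divided by model SE: √{[2 + (m − 1)ρ]/2}.
- Actual coverage of a nominal 95% interval: 2Φ(1.96/ratio) − 1.

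Example with m = 6 and ρ = 0.05: √{[2 + 5 × 0.05]/2} = √1.125 = 1.061.

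| Therapists per site | m | SE ratio, ICC 0.02 | SE ratio, ICC 0.05 | SE ratio, ICC 0.10 | Coverage, ICC 0.05 | Coverage, ICC 0.10 |
|---|---|---|---|---|---|---|
| 1 | 12 | 1.05 | 1.13 | 1.25 | 91.7% | 88.5% |
| 2 | 6 | 1.02 | 1.06 | 1.12 | 93.5% | 92.0% |
| 3 | 4 | 1.01 | 1.04 | 1.07 | 94.1% | 93.2% |
| 4 | 3 | 1.01 | 1.02 | 1.05 | 94.4% | 93.8% |
| 5 | 2.4 | 1.01 | 1.02 | 1.03 | 94.6% | 94.2% |

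At ICC 0 the ratio is 1. These are excesses over the model SE. In the extreme cell the true SE is 25% above the model SE, so the model SE is 1 − 1/1.245 = 20% below the true one.

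**In SD units.** Without clustering the 95% half-width is 1.96 × √(2/60) = 0.358 SD. At ICC 0.05 it should be 0.404 SD (m = 12), 0.380 SD (m = 6) or 0.364 SD (m = 2.4).

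**Check by simulation** (20,000 runs per setting, five sites, 12 patients per arm and site, site-adjusted analysis, ICC 0.05):
- One therapist per site: empirical SE 0.206 against model SE 0.181, coverage 91.4%.
- Two per site: ratio 1.07, coverage 93.4%.
- Four per site: ratio 1.03, coverage 94.4%.
- With ICC 0, coverage is about 95%.

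This confirms that the site term does not absorb therapist variance, even with one therapist per site.

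**For the later RCT.** With 12 patients per therapist and ICC 0.05, the design effect in the intervention arm is 1 + 11 × 0.05 = 1.55.

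**The case against.** The strongest reply is that little depends on this. Feasibility is the primary outcome in the Outcomes section, the model is exploratory, and no significance level or confidence interval is named. This stands: no confirmatory conclusion is at risk, and the effect estimate itself is not biased.

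Second, therapist differences may be small. There is a common manual, training in it, monthly supervision, and a standardised checklist on which "The therapists indicate which parts of the manual were carried out and which were not". The optional components are chosen by patient need, so they do not by themselves show that therapists differ. This also stands, and it is why the size can only be given as a range. It does not make an ICC of zero safe to assume, since therapists may be psychologists or physicians and the checklist itself anticipates uneven delivery.

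Third, a therapist variance estimated from 60 treated patients is very imprecise. Simulating a true ICC of 0.05, the central 95% of estimates runs from about −0.12 to 0.26 with ten therapists of six patients, and from about −0.07 to 0.24 with five of twelve. About 35% of estimates are zero or below in both cases. This stands and shapes the fix.

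Fourth, a separate analysis plan may add a therapist term. That is possible, but the article does fix its random effect and names site alone.

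Two stronger readings are not supported. A reader might infer that the intervals are certainly too narrow; that needs an ICC above zero and shared therapists, and neither is stated. A reader might also infer that the pilot's first-phase comparison is the only chance to estimate therapist variance; waitlist patients are treated later, and leaving a term out of a model destroys no data.

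**Conclusion.** The point holds conditionally. The site-only model leaves out the one source of clustering that differs between the arms. Its SE for the SF-12 contrast, and for the secondary outcomes analysed alike, is too small whenever the therapist ICC is above zero and therapists treat more than one study patient. Over the assumed range the shortfall runs from negligible to material. The 25% extreme requires one therapist per site together with ICC 0.10, and nothing in the article points to that combination. The consequence is limited to the precision, and the missing variance component, that the pilot hands on to RCT planning.

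**What to change.** Record the treating therapist for every treated patient. Therapists complete the session checklists, so this should be obtainable, but the article does not say that identity is stored or exported.

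Add to the analysis text a therapist random effect that acts in the intervention arm only (a partially nested model), with small-sample degrees of freedom, either as the main exploratory model or as a sensitivity analysis. Where the variance component cannot be estimated, report the SE over a stated range of assumed ICCs. Report the number of therapists, the caseload, and the ICC with its interval, using later-treated waitlist patients as well for the ICC.

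The cost is analysis wording and one data field, with no change to trial conduct. Intervals become somewhat wider and the ICC will be very imprecise. If sites have one therapist each, a site-by-arm random term is a costly substitute. It leaves about 4 degrees of freedom (t = 2.78 against 1.98), so at ICC 0.05 the interval is 2.78/1.98 × 1.13 ≈ 1.58 times as wide as planned, and the range of assumed ICCs is then more practical. Replacing the random site effect by a fixed one is optional and not part of this correction.

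### Adjusting for covariates only when observed baseline imbalance exceeds 20% leaves adjustment for baseline SF-12 to chance, at a small cost in precision and with intervals that are too wide

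*Protocol article*

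**What the plan says.** The rule stands in the protocol article, section on statistical methods for primary and secondary outcomes. The model is introduced there as follows: "In an exploratory fashion, mixed-effect linear regression analysis adjusted for study site (random effect) will be used". The response is each participant's SF-12 change from t1 to t2. Every covariate other than site is governed by one sentence: "Covariates will be adjusted for if misbalance in characteristics at baseline assessment is more than 20" per cent. Baseline SF-12 is not named as a fixed covariate.

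The rule carries over to the other scales: "In the same way, secondary outcomes will be analysed". The same section applies the primary-outcome method to the cytokine values as well.

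Three other places bear on the point. Under Sequence generation: "The randomization is stratified by study center". Under Sample size there are 60 participants per arm, and "Case numbers are based on feasibility within a pilot trial". Under Outcomes the purpose of the model is given: "an estimate of the effect size in preparation of an RCT will be conducted".

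**The concern.** Covariate adjustment in a randomised trial pays off through the covariate's relation to the outcome. The rule selects on something else. After proper randomisation, any baseline difference between arms is chance, and its size carries no information about prognostic value. The rule can admit an irrelevant variable that happens to differ and leave out a strong predictor that happens to be balanced. The baseline value of the outcome is the plainest case: it is collected from everyone at t1, yet it enters the model only if the arms happen to differ on it.

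At stake are the precision of the estimated effect and the calibration of its interval. Both feed the planning of the later RCT.

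**Working it through.** The article gives no alpha, power, effect size or SD, so there is no figure of its own to reproduce. The check asks what the rule does to the treatment effect when the covariate in question is the baseline value of the outcome.

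**From the document:** n = 60 per arm; response is the change score; covariate admitted only above 20% imbalance.

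**Assumed:** 20% means a standardised mean difference above 0.2; baseline SF-12 counts among the characteristics checked; baseline/follow-up correlation ρ = 0.3, 0.5 or 0.7; equal variances (SD = 1); no site effect; no dropout; two-sided 5% test.

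**Step 1, how often the rule triggers.** The baseline difference d has variance v = 2/60 = 0.0333 and SE 0.183. The threshold is a = 0.2/0.183 = 1.095 SEs. P(trigger) = 2(1 − Φ(1.095)) = 27.3%. In the other 72.7% of trials the plain change score is used.

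**Step 2, standard errors in SD units.**
- Always adjusted for baseline: √(v(1 − ρ²)).
- Under the rule: when untriggered, the estimate equals the adjusted one minus (1 − ρ)d. The variance is therefore v(1 − ρ²) + (1 − ρ)²·v·K, with K = (2Φ(a) − 1) − 2aφ(a) = 0.727 − 2 × 1.095 × 0.219 = 0.247.
- Example, ρ = 0.5: 0.0333 × 0.75 = 0.0250; 0.25 × 0.0333 × 0.247 = 0.00206; √0.02706 = 0.164, against √0.0250 = 0.158.

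| ρ | Always adjusted | Rule | SE ratio | Simulated: adjusted / rule | Simulated ratio |
|---|---|---|---|---|---|
| 0.3 | 0.174 | 0.185 | 1.064 | 0.175 / 0.188 | 1.07 |
| 0.5 | 0.158 | 0.164 | 1.040 | 0.159 / 0.165 | 1.04 |
| 0.7 | 0.130 | 0.133 | 1.022 | 0.131 / 0.133 | 1.02 |

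The simulation used 10,000 trials per correlation with no treatment effect.

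**Step 3, calibration.** In an untriggered trial the model reports the unconditional change-score SE, √(2v(1 − ρ)). But d is then known to be small, so the true spread is only √(v(1 − ρ²) + (1 − ρ)²·v·K/0.727). For ρ = 0.3 this is 0.216 reported against 0.189 true, a ratio of 1.14. For ρ = 0.5 the ratio is 0.183/0.167 = 1.09, and for ρ = 0.7 it is 0.141/0.134 = 1.05. The reported interval is too wide by that factor. In triggered trials the adjusted model is correctly calibrated.

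Approximate rejection under no effect is 0.727 × 2(1 − Φ(1.96 × ratio)) + 0.273 × 0.05:
- ρ = 0.3: 3.2% (simulated 3.2%)
- ρ = 0.5: 3.7% (simulated 3.9%)
- ρ = 0.7: 4.2% (simulated 4.3%)

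With fixed baseline adjustment the simulation gave 5.1%, 5.2% and 5.0%. Repeat runs gave 2.8 to 4.1% under the rule.

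**Step 4, bias.** The trigger depends only on |d|, which is symmetric about zero and independent of treatment. The estimate therefore stays centred on the true effect, and a repeat simulation gave mean estimates of about zero under no effect.

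**The case against.** The strongest case on the other side is that little harm is shown. The model is labelled exploratory, the Outcomes section makes feasibility primary, and the sample size rests on feasibility, so no confirmatory claim depends on it. Site is always in the model. The response is already a change score, so baseline is partly used whatever the trigger does. The estimate is unbiased and the precision loss is a few per cent. All of this stands, and it limits the point to a modest one. It does not rescue the rule, which gains nothing over fixed adjustment and costs something.

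A reader might infer three stronger things that the document does not support:
- **That the model is picked after looking at results.** The rule looks at baseline characteristics, not at t2 outcomes.
- **That the intervals are too narrow or false positives inflated.** The calculation shows the reverse.
- **That the rule is unusable because 20% is undefined.** Readings do differ: with 60 per arm, a binary characteristic at 50% prevalence exceeds 20 percentage points in 2.2% of trials (exact binomial), against 27.3% for a standardised difference above 0.2. But a journal article commonly leaves the measure and the list of characteristics to the full protocol or SAP, which are not shown, so that gap is not a finding. A definition there would not cure the point made here: selecting covariates by chance imbalance is fixed by the sentence itself.

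**Conclusion.** The point holds in limited form. The stated rule is a poor one because it ties adjustment to chance imbalance and not to prognostic value. Under the assumptions listed, it raises the SE of the effect by about 2 to 7% against always adjusting for baseline, and it makes a nominal 5% test reject in about 3 to 4% of null trials, with intervals that are too wide. There is no bias and no type I inflation.

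The size depends on assumed correlations and on the 0.2 SD reading. If the reading were such that baseline SF-12 hardly ever triggered, the estimate would approach the plain change score. Its SE exceeds the adjusted one by the factor √(2/(1 + ρ)), which is 1.24, 1.15 and 1.08 for ρ = 0.3, 0.5 and 0.7; the test would then keep its nominal level. The consequence is confined to the effect estimate that is to inform the later RCT, in an exploratory pilot analysis.

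**What to change.** - Delete the imbalance trigger.
- In the t1-to-t2 model for each outcome, always include the baseline value of that outcome together with study site, whatever the observed imbalance.
- If age (continuous), sex or other covariates are wanted, name them on prognostic grounds before outcome data are examined by arm. That is the workable deadline, because the Trial status section reports that recruitment ended in mid-June 2023 and baseline data therefore already exist. Record the date of the change.
- Show baseline balance descriptively, and report any further adjustment only as a sensitivity analysis.

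Cost: a change of wording and one degree of freedom per model for the baseline value. No new data are needed, since the questionnaires are already collected at t1 in both groups.

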**Methods and analysis:**

This pilot trial implements a multi-centre, 2-arm (N=120; allocation ratio: 1:1), parallel group, randomised controlled design. The pilot trial is designed to test the feasibility and estimate the effect of 1) a 12-session psychotherapeutic intervention compared to 2) a wait-list control condition on psychosocial needs as well as bodily and affective symptoms in patients suffering from Long/Post-COVID. The intervention uses an integrative, manualized, psychotherapeutic approach. The primary study outcome is health-related quality of life. Outcome variables will be assessed at three timepoints, pre-intervention (t1), post-intervention (t2) and three months after completed intervention (t3). To determine the primary outcome, changes from t1 to t2 are examined. The analysis will be used for the planning of the RCT to test the efficacy of the developed intervention.

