## Interventions

### Explanation for the choice of comparators

Due to the randomized assignment to either the intervention group or the control group, any systematic differences and changes regarding symptom burden should be attributed to group affiliation and having received the psychotherapeutic treatment or not. As controls, a waiting list group was chosen as not offering the intervention to controls at a later time point would likely result in poor participation.

During the trial, both study groups are allowed to use regular medical care for Long/Post-COVID-symptoms, i.e. general practitioners or medical specialists (e.g. neurologists, nephrologists, cardiologists or physiotherapists). Participants who initiate psychotherapeutic treatment other than within the study intervention will be excluded.

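### The t2-to-t3 stability analysis, read literally, repeats the between-arm model in a period when the wait-list arm appears to be in therapy, and conflicts with the Outcomes section

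*Protocol article*

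**What the plan says.** The section on statistical methods for primary and secondary outcomes starts with descriptive summaries. It then gives one inferential tool, exploratory in status: "mixed-effect linear regression analysis adjusted for study site (random effect) will be used to check for differences between intervention and control groups" in the intraindividual t1-to-t2 difference in SF-12 quality of life. Secondary outcomes follow the same approach. The next sentence is: "These analyses will be also conducted to assess stability of changes i.e. comparing outcomes at t2 and t3". No other model is named for t3.

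The Outcomes section assigns the time points differently. On the arm comparison it says: "The analysis of intervention effects compared to control group is only conducted at the end of the intervention in the primary intervention group". For what comes after, it allows two uses. One is a check of the early against the late group: "Later measurements are only used to assess if the effects in the early and late (after waiting) intervention group are similar". The other concerns durability, namely "whether the effects are maintained after the intervention phase".

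The section on the choice of comparators explains that controls are on a waiting list because "not offering the intervention to controls at a later time point would likely result in poor participation". The text does not say when their therapy starts, and the participant schedule (Figure 1) is not available in the copy reviewed.

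**The concern.** Stability of an effect is a question about people who have finished therapy: do they keep what they gained? A between-arm difference in t2-to-t3 change answers that only if the comparison arm stays untreated over the same months. If the comparison arm is in therapy then, the contrast sets follow-up after therapy against active therapy. The better the therapy works for the wait-list arm, the more negative the result, whatever happens to the early group.

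At stake is what the pilot reports about durability, which could feed into the planned RCT. The two sections also give an analyst conflicting instructions for t3.

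**Working it through.** **Step 1. What is repeated.** The sentence on stability points back to the analyses just described. The only inferential one is the between-arm model on change. Applied to t2 to t3, its estimate is

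contrast = (mean t3 − t2 change, early arm) − (mean t3 − t2 change, wait-list arm).

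**Step 2. Are controls treated in that window?** This is inferred, not stated.

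- Only three questionnaire assessments are listed (t1, t2, t3), for both groups. The Outcomes section wants to compare the effect in the early and late groups. The only listed assessment after t2 is t3, so the late group's effect is observable only if its therapy falls at least partly between t2 and t3.
- Recruitment ended in mid-June 2023 (Trial status) and the last follow-up is planned for the end of November 2023 (Intervention description). A control enrolled on 15 June who waits 12 weeks reaches 7 September, and 12 weeks of therapy from there end on 30 November.
- How much therapy is complete at t3 is less certain. The Outcomes section puts t3 six months (about 26 weeks) after baseline, whereas the abstract puts it three months after the intervention is completed. For the early arm these roughly agree. For a control starting at t2, therapy ends at 12 + 12 = 24 weeks, or at 14 + 14 = 28 weeks if both periods use the permitted two-week prolongation. Therapy could therefore finish shortly before or shortly after a six-month t3.

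**Step 3. Expected value.** Let d be the true effect in SD units, fully maintained in the early arm (change 0), and let f be the share of d that controls have gained by t3. Then

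contrast = 0 − f·d = −f·d.

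**Step 4. How often it would be significantly negative.** The sample size section bases the total of 120 (60 + 60) on feasibility and gives no effect size, SD, correlation, significance level or dropout. There is no power figure to reproduce, and the following are assumptions: 60 analysed per arm, within-person correlation r of 0.5 to 0.7, two-sided 5%.

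SE = √[2(1 − r) × 2/60], which is 0.183 SD at r = 0.5 and 0.141 SD at r = 0.7.

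P(significantly negative) ≈ Φ(f·d/SE − 1.96).

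Example: d = 0.5, f = 1, r = 0.5 gives 0.5/0.183 = 2.74 and Φ(0.78) = 0.78.

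| d (SD) | No control gain | Half gain | Full gain |
|---|---|---|---|
| 0.2 | about 2.5% | 8-11% | 19-29% |
| 0.3 | about 2.5% | 13-18% | 38-56% |
| 0.5 | about 2.5% | 28-42% | 78-94% |
| 0.8 | about 2.5% | 59-81% | 99-100% |

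Within each cell the lower figure is for r = 0.5 and the higher for r = 0.7. With 48 per arm (20% loss), the full-gain figures fall to 31-48% at d = 0.3 and 69-89% at d = 0.5.

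**Step 5. Simulation check.** In 300 simulated trials with five sites of 24, site as random effect, d = 0.5, r = 0.5 and full gain in controls, the between-arm t2-to-t3 contrast averaged −0.515 SD and was significantly negative in 78% of runs. The early arm's own t2-to-t3 change averaged −0.01 SD. The within-arm quantity shows the maintenance that is truly present; the between-arm quantity does not.

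**The case against.** The strongest reply is that the Outcomes section already gives t3 the right job. It confines the arm comparison to t2 and names maintenance as a use of later data. If that section governs, the misleading contrast is never produced as a stability result. The sentence on stability is also loosely worded: its gloss names two time points, not two arms, and the paragraph opens with descriptive summaries. It could mean the same methods applied within the early group. The controls' start date is not stated, and the analysis is exploratory in a pilot whose primary outcome is feasibility.

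Much of this stands, and it limits the severity. It does not remove the point. The methods section is where an analyst looks for the model, and the only inferential model there is the between-arm one. That the Outcomes section states a different purpose is the conflict itself. Nor is this detail left to a fuller document: the article states a rule that does not fit its own stated aim.

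A reader might go further and infer that a maintained effect will be reported as lost. The documents do not support that. It would require the literal reading to prevail over the Outcomes section, controls to have gained substantially by t3, and the result to be interpreted as loss despite the descriptive summaries alongside.

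**Conclusion.** The stability sentence is wrong as written and conflicts with the Outcomes section. Followed literally, it estimates the early group's change minus the controls' gain, so a fully maintained effect could look like a loss of up to the full treatment effect.

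The chance of a significantly negative result depends on assumptions the documents do not supply. It runs from about 2.5% if controls have gained nothing by t3 to more than 90% in the less favourable scenarios, so no single figure should be quoted as the risk. That controls are treated between t2 and t3 is a well-supported inference, but still an inference.

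Severity is moderate. The analysis is exploratory, and the t1-to-t2 effect estimate that serves the planned RCT is unaffected.

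**What to change.** Reword the stability sentence in the statistical methods section to match the Outcomes section:

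1. Maintenance is the within-arm t2-to-t3 change in the early intervention group, reported with a 95% confidence interval and with site as random effect.
2. The early-versus-late comparison uses each group's own pre-to-post-therapy change (early t1 to t2, late t2 to t3) and is labelled as a non-randomised comparison across different periods. This keeps the comparison that the Outcomes section plans.
3. The between-arm difference in t2-to-t3 change is not used as a measure of stability or efficacy.

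In the same edit, state when the wait-list arm's therapy falls relative to t2 and t3, and reconcile the two definitions of t3 for that arm, because item 2 depends on t3 coming after the late group's therapy.

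The cost is wording in the protocol or analysis plan. The data are already scheduled for collection, and neither the sample size nor the t1-to-t2 analysis changes.
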